### Method of Assignment/Randomization

We will use the REDCap automated randomization tool to assign participants into one of two study arms 1:1 and stratified by: (1) site (AL or CT) to balance arms by potentially unmeasured factors that differ by site; (2) past 6-month stimulant use, given high prevalence of stimulant use in this population and association of stimulant use with reduced MOUD retention; [41] and (3) receipt of MOUD at baseline. We selected these strata because we hypothesize these are important effect modifiers and that the implementation strategy will differentially affect these groups. Randomization will be irrespective of baseline decisional preference for PrEP because we expect nearly all will have high interest in PrEP after the decision aid (80–90% based on our pilot clinical trial) [34], but if there are differences in decisional preference between the two groups, we will assess this in the analysis.

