## Statistical analyses

### Sample size

The study is powered on the primary outcome, PrEP initiation. The null hypothesis (H0) is that the proportion of participants initiating PrEP in the Athena arm will be the same as in the decision aid-only arm, whereas the alternative hypothesis (H1) is that the proportion of participants initiating PrEP in the Athena arm will be higher than those in the decision aid-only arm. Based on our clinical trial of a decision aid [33], we anticipate ~ 20% of decision aid-only participants will achieve the primary outcome. Based on our demonstration project of eHealth for PrEP for WICL [36], we anticipate 40–50% of Athena participants will achieve the primary outcome. A total sample size of 212 (106 in each group) would achieve 90% power to detect a 20% absolute difference between the two arms. The proportion in the Athena arm is assumed to be 20% under the null hypothesis and 40% under the alternative hypothesis. The proportion in the decision aid-only arm is < 30%. We will inflate the sample size by 15% to account for attrition and will plan to enroll 250 participants total across 2 sites, which is highly feasible. Though we attempt to minimize missing data by having an objectively measured outcome, we have considered additional plans for missing data that include performing both intention-to-treat and per protocol analyses and performing multiple imputation sensitivity analyses if appropriate.

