### Primary analyses

We will evaluate the effect of the Athena strategy, as compared to the decision aid-only (active control) in terms of the primary outcome, PrEP initiation. We will first conduct a descriptive analysis to characterize the study sample in terms of baseline characteristics overall, by treatment arm, and by site. The primary outcome (proportion of participants initiating PrEP) will be compared by treatment arm, site, and race/ethnicity using chi-square techniques. Using an intention-to-treat approach, we will build a multivariate logistic regression model of PrEP initiation; participant characteristics will first be evaluated in univariate models and, if significant at a more liberal p-value threshold, will be used in the multivariate model. In a per-protocol analysis, we will exclude time periods during which individuals are incarcerated during study follow-up, and thus removed from community exposure. The log-rank chi-square test (Kaplan-Meier survival analysis) will be used to compare time to first PrEP visit and time to PrEP initiation between the two arms. We will use descriptive analyses to characterize the PrEP care continuum for the entire sample over 12 months of follow-up, stratified by randomization arm and comprising the following steps [29]: HIV risk, PrEP awareness, completed PrEP visit encounter, PrEP initiation, PrEP adherence, and PrEP care retention by 1-, 3-, and 6-months post-baseline. We will describe engagement in the OUD treatment cascade both overall and by study arm, in terms of treatment initiation, retention, and substance use remission. Participant profiles will be created based on baseline characteristics (within each treatment arm) to assess changes in outcomes over time by site, study arm, and site by study arm. Depending on the distribution of such profiles, we will conduct a latent class analysis to explore characteristics of individuals as they relate to the established profiles. We will assess substance use over time with repeated measures and model using generalized estimating equations (GEE), by study arm and by site. We will assess for the complexity of SUD treatment (e.g., court-mandated vs. voluntary, behavioral vs. MOUD) and explore changes in treatment engagement over time, depending on substance use treatment modality. We will similarly describe diagnosis and treatment engagement for comorbid Hepatitis C and sexually transmitted infections over the 6-month period of observation.

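### Profiles are to be created separately within each arm and then used to compare the arms; if they are data-driven, one pooled derivation is the safer plan (minor)

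*Protocol article*

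**What the plan says.** All of the relevant text is in the protocol article, Statistical analyses, Primary analyses.

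- Derivation: "Participant profiles will be created based on baseline characteristics (within each treatment arm) to assess changes in outcomes over time by site, study arm". The parenthesis qualifies how the profiles are made.
- Use: the same sentence names the comparisons the profiles serve, which are the sites, the arms and the combination of the two.
- Follow-on step: if the way the profiles turn out allows it, "we will conduct a latent class analysis to explore characteristics of individuals as they relate to the established profiles". This step is conditional and takes the profiles as already formed. It does not say whether the latent class model is fitted within arm or on all women.

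The article gives no pooled definition and no rule for pairing a profile in one arm with a profile in the other. It does not name the profile variables or the method of forming profiles.

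Two design facts bear on the point. Under Method of Assignment/Randomization, the tool will "assign participants into one of two study arms 1:1 and stratified by" site, recent stimulant use and MOUD at baseline. Under Sample size, the team "will plan to enroll 250 participants total across 2 sites".

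**The concern.** A comparison of arms within a subgroup is a like-for-like randomised comparison when membership of the subgroup does not depend on the arm. A rule built on baseline data from both arms together, without using the allocation, meets that condition. Two rules fitted separately in each arm may not: a woman with given baseline data could fall in one profile if allocated to Athena and in another if allocated to decision aid only.

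Stratified 1:1 allocation balances the arms on three factors. It does not make two separately fitted partitions agree. Splitting also gains nothing, because baseline characteristics cannot be affected by the arm, and it halves the sample on which each partition rests.

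What is at stake is how a difference between arms within a profile is read. Part of it could reflect different profile boundaries in the two arms.

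**Working it through.** **1. Size of each derivation.** The plan's numbers reproduce. For 20% versus 40% with 90% power, assuming a two-sided 5% level (the article states none), the unpooled formula gives

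n per arm = (1.960 + 1.282)² × (0.2×0.8 + 0.4×0.6) / 0.20² = 105.07, so 106 per arm and 212 in total.

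Then 212 / (1 − 0.15) = 249.4, so 250, and 250 / 2 = 125 women per arm. No sample-size figure is disputed; 125 is simply the number behind each within-arm derivation.

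**2. Mechanism.** For profile j, the observed arm difference is

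D_j = effect in j + [mean prognosis under the Athena-arm rule − mean prognosis under the control-arm rule] + sampling error.

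With one common rule the bracket is zero. With two rules it is random. With no effect and the same method in both arms it averages zero over repeated trials, so it adds variance and not bias.

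**3. Null simulation, varying how distinct the groups are.** All settings are assumptions: 125 per arm, no treatment effect, four baseline variables of which one is prognostic, three k-means profiles paired across arms by their order on the prognostic variable, 400 trials per setting, and a two-sided 5% two-proportion test in each profile.

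| True groups | Same woman, same profile under both arms' rules | False positives, separate | False positives, pooled | Gap (points) | SD of D_j, separate / pooled |
|---|---|---|---|---|---|
| none | 42% | 10.6% | 6.8% | 3.8 | 0.122 / 0.105 |
| weak | 62% | 10.8% | 4.3% | 6.5 | 0.123 / 0.097 |
| moderate | 94% | 7.6% | 5.5% | 2.1 | 0.099 / 0.092 |
| very distinct | 99.8% | 3.6% | 3.5% | 0.1 | 0.072 / 0.072 |

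Each rate rests on at most 400 × 3 = 1,200 tests, so its simulation standard error near 5% is about √(0.05×0.95/1200) = 0.6 points. The gap matters more than the decimals. Agreement of 42% is not far above the one in three that three arbitrary labels would give, so the crude pairing rule contributes to the first row.

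**4. Null simulations with a closer pairing rule.** Again 125 per arm, now with six baseline variables, a prognostic factor, k-means with three or four profiles, and pairing by centroid. One run gave 7.2-8.0% (separate) against 4.2-4.8% (pooled). A second run gave 8.1% and 7.4% against 4.8% and 4.5% in its two settings.

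**5. Fixed-rule profiles.** When the same pre-set rule was applied in each arm, the per-profile rate was 4.7-4.9%, which is nominal.

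**6. Site-by-arm contrasts within profiles.** Separate against pooled: 6.0% against 5.2% (three profiles) and 6.5% against 6.8% (four profiles) in one set of 600 null trials; 6.3% against 6.5% and 5.1% against 5.9% in another set. There is no consistent excess. Within an arm both sites share the same boundaries, so the boundary mismatch largely cancels.

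**7. Average bias.** The mean arm difference under the null was below 0.5 percentage points with either derivation.

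**The case against.** The best reply is that the article never says the profiles are clusters. Latent class analysis comes later and only conditionally, so the profiles may be simple rule-based groups. The randomisation factors would be natural ones. A fixed rule applied in each arm is the same rule, and nothing goes wrong. The parenthesis might also mean only that results are laid out by arm. How profiles are built is detail that a condensed article may leave to a fuller document, and the missing pairing rule is not in itself an error. The per-profile test in the simulations was also supplied for this check; the article does not plan it.

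Much of this stands. It makes the concern conditional on data-driven profiles and makes the false-positive rates illustrative. It does not remove the point, because the article states that the profiles are created within arm and used by arm. If fixed rules or a by-arm display were meant, the sentence misdescribes the intention and still needs correcting.

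A reader might infer four stronger things that the documents do not support:

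- That the profile comparisons lose the protection of randomisation altogether. The average bias is zero; the harm is extra variance and non-comparable groups in the one trial that is run.
- That site-by-arm findings are distorted in the same way. The checks showed no such excess.
- That these profiles are meant to show for whom Athena works. The article gives no such purpose; the effect modifiers it hypothesises are the randomisation strata.
- That the latent class step is a second instance. The article says "we will conduct a latent class analysis to explore characteristics of individuals as they relate to the established profiles", without saying that the model is fitted within arm.

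**Conclusion.** The point holds as a minor one. As written, profiles are derived inside each arm and then used to compare arms. If the derivation is data-driven and the groups are not very distinct, a profile of the same name need not contain comparable women in the two arms. Under the assumed settings the per-profile false-positive rate for an arm difference is then roughly 7-11%, against about 4-7% with pooled derivation.

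These figures depend on invented choices of variables, algorithm, number of profiles, pairing rule and test, because the article specifies none of them. They show the direction and plausible size of the problem; they do not predict this trial's error rate.

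Although the text sits under Primary analyses, the profile work is exploratory in character. The intention-to-treat comparison of PrEP initiation, the log-rank comparisons and the sample size do not use the profiles and are unaffected.

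**What to change.** Derive the profiles once, from the baseline data of all randomised women and blind to arm, and apply that single definition to both arms. Do the same for any latent class model. Delete the parenthesis about treatment arm from the derivation step. Results may still be displayed by arm, by site, and by site and arm. If differences between profiles are of interest, assess them through profile-by-arm terms using the common profiles.

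If the profiles are in fact fixed rules, stating those rules and saying that they are identical in both arms is enough.

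The cost is a change of wording. No new data are needed, the analysis is no more work, the sample size does not change, and the sample used to form profiles rises from about 125 to 250.

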### Secondary analyses

We will model individual- and population-level effects on averted HIV infections and quality-adjusted life-years (QALY); then we will use qualitative analysis guided by the Proctor Framework to understand process measures important to potential Athena scale-up [38]. For the modeling component of the study, we will employ state transition Markov modeling techniques to estimate long-term outcomes in terms of averted HIV infections and QALY gains at the individual level. Markov models offer a powerful tool to simulate individual transitions through a set of mutually exclusive states over time [47]. The model will include states characterized by HIV status and PrEP enrollment, as well as MOUD enrollment. Health utility weights of different health states will be estimated from literature [48]. Population-level effects from scaling up PrEP using the Athena strategy and decision aid-only will be evaluated using compartmental dynamic transmission modeling techniques [49]. We will stratify a hypothetical population by their behavioral characteristics predictive of HIV transmission risk and run the model assuming different intervention scale-up levels. In the base case analysis, we will run the models over a 10-year time horizon and will explore the sensitivity to this timeframe by running the models over 5- and 15-year horizon. Descriptive statistics will be used to evaluate structured survey data. For the nominal group technique (NGT) component, as we have done previously [50–54], we will tabulate votes to immediately rank priorities. Once group ranking is completed, we will undertake a thorough discussion to ensure the ranking has face validity to hear minority voice perspectives. If there is lack of clarity in the NGT ranking and for in-depth interviews, the transcript will be reviewed by two independent reviewers to decide if the responses are convergent or divergent, and where there is disagreement a third person will break the tie [55, 56]. NGT and interview transcripts will be analyzed separately for each purpose in NVivo based on modified grounded theory methods [57] and thematic content analysis [58] involving an iterative process of reading transcripts, identifying themes, and forming a coding scheme. To imbue sense into the thematic codes, analysis will be guided by the Proctor implementation outcomes framework [38]. Context will be an important consideration at all levels of the framework, and we will specifically assess for key site differences in organizational/process outcomes from these multi-level perspectives because similarities and differences by site are important for implementation and to ensure there is generalizable knowledge for future scale-up.

Once the findings are compiled, to move from evaluation to action, we will convene a stakeholder policy symposium at each site to present findings and discuss incorporation of findings into Athena sustainability plans in each state. Findings will be presented to community advisory boards at each site at the end of the study to identify opportunities to advocate for systems change. We will invite policy-maker participants (e.g., state health officers, state Medicaid policy-makers) to join the investigative team to produce a white paper on policy issues related to the Athena strategy of eHealth delivery of integrated PrEP/MOUD.

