## Methods

### Study design

This study is a multi-site two parallel-arm unblinded randomized clinical trial comparing the “Athena strategy,” a low-demand model that includes a PrEP decision aid and eHealth delivery of integrated PrEP/MOUD, to a PrEP decision aid-only in terms of patient-level engagement in the PrEP care continuum among WICL with OUD, considering key participating site differences. The primary clinical outcome is PrEP initiation over six months; secondary outcomes are 6-month PrEP retention and engagement in the OUD treatment cascade. We will assess for the complexity of SUD treatment (e.g., court-mandated vs. voluntary; behavioral vs. MOUD) and changes in treatment engagement over time. Exploratory outcomes include diagnosis and treatment of comorbid Hepatitis C and sexually transmitted infections. We will also assess scale-up potential of the Athena strategy in terms of modelled long-term outcomes and how stakeholders interact with eHealth for integrated PrEP/MOUD in WICL in two diverse epidemiological and implementation contexts, using standardized definitions of implementation outcomes [38]. In a state transition model, we will estimate averted HIV infections and quality-adjusted life-year (QALY) gains at individual and population levels over a 10-year time horizon [39]. We will incorporate multi-level perspectives on implementation through focus groups using nominal group technique (NGT), structured surveys, and in-depth interviews.

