### Eligibility criteria

Research assistants will contact all interested individuals to complete a more detailed study eligibility screen in REDCap. Referred clients will be assessed for the following study eligibility criteria: (1) cis-women; (2) ages 18-59y (because they experience the highest HIV risk); (3) have access to a working mobile or landline phone; (4) CL-involved (currently on probation, parole, intensive pretrial or community supervision, or are within 12 months after release from prison/jail;) (5) meet clinical criteria for PrEP; and (6) have OUD (regardless of baseline MOUD treatment status), as determined by a SAMHSA-recommended single-item screening question: *How many times in the past year have you used an illegal drug or a prescription medication for nonmedical reasons?* and followed by confirmation of OUD using the validated Rapid Opioid Dependence Screen (RODS) [40]. 

Referred clients will be excluded if they are: (1) unable or unwilling to provide informed consent; (2) pregnant or breast-feeding; (3) currently taking PrEP at the time of study enrollment; (4) not comfortable conversing in English or Spanish; or (5) test positive for HIV. There is no exclusion based on health or technology literacy, homelessness, trauma, substance use or psychiatric disorders, and we will address these factors in our intervention and analysis.

As part of screening for study eligibility, individuals will undergo rapid point of care screening for HIV with the ORAQUICK Advance^®^ Rapid HIV-1/2 Antibody Test. Participants who screen negative meet inclusion criteria. Participants who have an indeterminate or positive result for either will be sent for confirmatory testing and referred for HIV care if confirmed positive. Potential participants will also be screened for pregnancy with a urine hCG. Participants testing HIV + or pregnant will be counseled, referred for care, and excluded from the study.

We will verify CL involvement using publicly available websites and by directly contacting supervising officers with a signed release of information; all participants recruited from “community corrections,” parole, probation, or closed detention settings are already known to be CL-involved. Of note, we will only enroll women who are residing in the community. Women who are informed about the study during incarceration and interested in participating can enroll following return to communities; no one will be enrolled while they are incarcerated.

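### QALY gains accrue only to the model horizon (10 years, 15 at most), so the lifelong benefit of an averted HIV infection is understated in outputs described as long-term

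*Protocol article*

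**What the plan says.** The Study design section of the protocol article ties the horizon to the QALY outcome itself: "we will estimate averted HIV infections and quality-adjusted life-year (QALY) gains at individual and population levels over a 10-year time horizon".

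The Secondary analyses section gives the purpose of the individual-level Markov model as "to estimate long-term outcomes in terms of averted HIV infections and QALY gains at the individual level". On its structure it says: "The model will include states characterized by HIV status and PrEP enrollment, as well as MOUD enrollment". A separate dynamic transmission model covers the population level. For both models the section then states: "In the base case analysis, we will run the models over a 10-year time horizon and will explore the sensitivity to this timeframe". The two alternatives it names for that check are 5 and 15 years.

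No lifetime run is described, and no QALY value is attached to the state a woman occupies when the run ends. Nothing says that such a value is excluded.

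The Eligibility criteria section admits women of "ages 18-59y (because they experience the highest HIV risk".

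**The concern.** A single horizon does two jobs. It sets the period over which uptake and infections are simulated, and it sets the date at which QALYs stop being counted. Ten years is a reasonable choice for the first job. For the second it is short, because HIV infection lasts for life. At the midpoint of the eligible age range, (18 + 59) / 2 = 38.5 years, the base case stops at age 48.5 and the longest run at 53.5. For an 18-year-old the stopping ages are 28 and 33.

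An infection averted at year t is therefore credited with at most 10 − t years of benefit in the base case. What follows is left out, although the outputs are called long-term.

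The modelled results serve to judge scale-up potential (Study design). The study's findings are to be taken to policy symposia, and policy-makers are to be invited to help write a white paper (end of Secondary analyses). A reader there could take a 10-year figure for the whole health gain.

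**Working it through.** The document states no QALY total and no credited years per infection, so there is no plan figure to reproduce. The check asks what share of lifetime credit the stated horizons can capture.

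**Inputs from the document:** horizon H = 10 years in the base case, 5 and 15 years as sensitivity runs; ages 18 to 59.

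**Assumptions, not in the document:** remaining life L = 20, 30 or 40 years from model start; discount rate r = 0 or 3%; a constant yearly QALY loss with HIV, which cancels from the ratio; an averted infection stays averted; the timing of averted infections as given below.

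**Even timing over 0 to H, undiscounted.** Mean credit to the horizon is H/2 = 10/2 = 5 years. Mean credit to end of life is L − H/2 = 15, 25 and 35 years. The shares are 5/15 = 33%, 5/25 = 20% and 5/35 = 14%.

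**Even timing, 3% discount.** Mean credit to an end point E (E = H or E = L) is (1/r) × [(1 − e^(−rH))/(rH) − e^(−rE)].

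- For H = 10, (1 − e^(−0.3))/0.3 = 0.864.
- With E = 10: (0.864 − 0.741)/0.03 = 4.10 years.
- With E = 20, 30 and 40: 10.50, 15.25 and 18.76 years.
- Shares: 39%, 27% and 22%.

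**All infections averted in the first 6 months.** The mean t is 0.25 years, so undiscounted credit to the horizon is 10 − 0.25 = 9.75 years against L − 0.25 = 19.75, 29.75 and 39.75 years. At 3% the credit to the horizon is 8.39 years against 14.79, 19.53 and 23.04 years.

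Share of lifetime credit captured by the 10-year run:

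| Timing | Discount | L = 20 | L = 30 | L = 40 |
|---|---|---|---|---|
| Even over 10 years | 0% | 33% | 20% | 14% |
| Even over 10 years | 3% | 39% | 27% | 22% |
| First 6 months only | 0% | 49% | 33% | 25% |
| First 6 months only | 3% | 57% | 43% | 36% |

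**Intermediate front-loading.** If averted infections decline exponentially at 0.1, 0.3, 0.5 or 1.0 per year, mean undiscounted credit in the 10-year run is 5.8, 7.2, 8.1 or 9.0 years. Each lies between the even case (5) and the 6-month case (9.75).

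**What the other horizons would show.** Under even timing, total QALY-years are proportional to H × H/2: 12.5, 50 and 112.5 for 5, 10 and 15 years, a ratio of 0.25 : 1 : 2.25. Credit per averted infection would be 2.5, 5.0 and 7.5 years. The gain would plainly still be rising at 15 years. Even so, the 15-year run captures only 7.5/(L − 7.5) = 7.5/12.5, 7.5/22.5 and 7.5/32.5, that is 60%, 33% and 23% of undiscounted lifetime credit.

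**The case against.** The best defence is that the horizon is declared and varied in both directions, so the result is an openly stated 10-year gain. The truncation is conservative, and the article describes no cost-per-QALY ratio or threshold that it could tip. A fuller modelling plan may also hold an end-of-horizon value. Much of this stands. It makes the matter one of interpretation and keeps it away from the trial's primary result. It does not remove the gap between outputs called long-term and an accrual period that ends at 10 or 15 years, both of which the article itself states.

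The age argument has a limit too. The range 18 to 59 is trial eligibility, while the population-level model uses a hypothetical population whose ages are not given.

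Three stronger readings are tempting, and the document does not support them:

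- **That each averted infection earns about 5 years.** This holds only if infections are averted evenly over the horizon. Across the even and front-loaded timings tested, the mean runs from 5 to 9.75 years, and the document says nothing about timing or about PrEP persistence beyond the 6-month follow-up.
- **That the 5- and 15-year runs conceal the truncation.** Averted infections and QALY gains are both outputs, so dividing one by the other would expose it.
- **That MOUD benefit is counted in full while PrEP benefit is cut, so the model misattributes the gain.** The text says only that MOUD enrollment is among the model states. MOUD benefit continuing past the horizon would be cut at the same point, and no split of QALYs by component is promised.

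**Conclusion.** The point holds as an understatement of the QALY gain from averted infections. Under the stated assumptions the 10-year run captures about 14–33% of undiscounted lifetime credit with even timing, 22–39% with even timing at 3%, and 25–49% undiscounted if all infections are averted in the first 6 months. The mildest combination tested, early aversion with 20 years remaining and 3% discounting, still loses 43%.

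The size rests on timing, remaining life and discount rate, none of which the document gives. It also rests on infections being averted and not merely postponed; if some women acquire HIV after year 10, lifetime credit is smaller and the captured share larger. The direction is the same in every case tested.

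The planned 5- and 15-year runs would signal strong horizon dependence without measuring the lifetime loss. Counts of infections averted within the horizon, the primary outcome and the sample size are untouched. This is a worthwhile, inexpensive improvement to a secondary modelling analysis.

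**What to change.** Keep 10 years as the period over which PrEP and MOUD uptake and HIV infections are simulated. Add a scenario in which each infection averted in that period is credited with discounted remaining-lifetime QALYs. State the discount rate, the survival inputs with and without HIV, and the assumption made about HIV risk after year 10. Report this figure beside the within-horizon one, and label the latter a 10-year QALY gain wherever it appears. The 5- and 15-year runs can stay as planned.

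The cost is one extra model run and literature survival inputs. The drawback is reliance on survival extrapolated beyond the simulated period, which readers can judge because both figures are shown. Trial conduct and data collection do not change.
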